#### Measures

##### Demographics and Background Information

Information collected at baseline will include age, sex and gender, race, weight and BMI, education level, medications, history of psychological symptoms, history of psychological treatment, and history of substance use and substance use treatment.

##### Alcohol Use

We will measure past 30-day alcohol use, similar to other studies, using adapted items from the Behavioral Risk Factor Surveillance System Questionnaire [28]. Participants will be shown a diagram and description of a standard drink and report the number of days they consumed any alcohol in the past 30 days (0-30). The primary outcome is drinking status (ie, whether alcohol was consumed in the past 30 d). For those who endorse at least 1 drinking day, they will also report on the number of average standard drinks per day, the highest number of drinks in a day, the number of days they consumed 4 or more drinks, and the number of days they perceived that they were drunk. The presence of hazardous alcohol use will be measured with the Alcohol Use Disorder Identification Test-Consumption [29]. This version was chosen because it is shorter than the original Alcohol Use Disorder Identification Test, while still providing a reliable assessment of drinking behavior [29,30]. An Alcohol Use Disorder Identification Test-Consumption score of 3 or greater for women and 4 or greater for men indicates high risk for hazardous drinking.

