CBI session 1 begins with an importance ruler, in which participants are asked, “How important is it for you to avoid alcohol use?” and they respond on a scale of 0 (not at all important) to 10 (very important). The narrator then presents a brief educational component (facts about alcohol use), which incorporates a gender- and race-matched video vignette of a patient who develops an AUD after MBS. Education includes information tailored to this patient population regarding: (1) the new, increased risk for AUD after MBS, (2) reasons for the increased risk (ie, the physiological changes postsurgery and how alcohol is metabolized differently), (3) the health risks of alcohol use (eg, impact on nutrition, weight loss, and physical health), and (4) the “pros” of avoiding alcohol use (eg, impact of alcohol use on MBS, weight loss, mental health, success at work and school, and preventing injury). Participants are again asked about the importance of avoiding alcohol use using the importance ruler. Content is thereafter tailored to each individual’s importance rating. Participants who do not think it is important to avoid alcohol (indicated by scores 0-3) receive intervention content that mirrors phase I of MI (ie, building motivation to abstain or reduce drinking behavior) [12]. Those who are “not sure” (as measured by scores 4-7) receive content on identifying ways to know when it is time to change. For both groups (ie, 0-3 and 4-7), the narrator presents information to evoke change talk (ie, ideas that relate to making behavior changes) [11,12]. Specifically, the narrator asks questions, such as, “If you did to decide to make a change, what would be the best part about having cut down or quit?” “Picture things a year from now. How would you like them to turn out?” and “If you did decide to make a change, what are some reasons you might succeed?” For each of these prompts, participants are presented with myriad response options to choose from, including an open text box, and their responses are reflected by the narrator. A similar approach was successful in increasing confidence for change within a technology-based intervention [19]. Participants who endorse a high level of importance (scores 8-10) are asked about reasons for change, how they might change, and who might help them. All responses that reflect change talk (ie, interest in changing, identification of how they will know it is time to change, and reasons for change) are reinforced with affirmations and reflections. This combination of closed and open questions to elicit change talk, reflections of change talk, and affirmations is among the strongest predictors of further change and commitment talk within MI frameworks [20-23]. The selected change talk from this first CBI session provided by the participant is used in the subsequent SMS text messaging component, which takes place after CBI session 2.

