#### Participants and Procedures

We plan to enroll 60 participants who underwent MBS 3 and 18 months before the invitation to participate in the study. This time frame was selected to engage patients who have not yet begun postoperative drinking (most reinitiate between 6 and 12 months postoperatively) [7] and to also engage individuals who began drinking, but are unlikely to have already developed AUD because the risk increases approximately 2 years postoperatively [4]. Patients who underwent MBS at a single institution within this time frame will be sent an email invitation to complete a web-based eligibility survey. Individuals will be eligible to participate if they engaged in alcohol use before MBS, have access to the internet to complete the CBI, and have a cellular phone that can receive SMS text messages. Eligible individuals will be contacted by our study team and provided with a detailed description of the study. Patients will be allowed to ask any questions to the study team and will provide a signature to document their informed consent. Once patients provide informed consent, participants will complete their baseline assessment through a web-based, secure, and Health Insurance Portability and Accountability Act–compliant program (Research Electronic Data Capture). Participants will then be randomized to the intervention group or the treatment-as-usual control group (ie, MBS-related follow-up care) using urn randomization, separating participants by sex and time elapsed since MBS. Participants will complete assessments 1 month after baseline, at the postintervention evaluation (ie, 3 months following baseline), and at the 6-month follow-up through Research Electronic Data Capture. Participants randomized to the intervention group will also complete an exit interview to obtain feedback about the intervention. Participants will be compensated US $50 for each assessment completed.

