#### Analytic Plan

We will examine the frequencies of our feasibility, adherence, and acceptability variables. Although the primary focus is on feasibility and acceptability, we also plan to examine the direction of effects on outcomes. Our primary outcome is alcohol use. We will conduct chi-square and logistic regressions for categorical outcomes, and analysis of covariance for continuous variables (controlling for baseline measurements) to examine differences in outcomes between the intervention and control groups at the postintervention evaluation. For the 6-month follow-up, logistic regression will be used for the categorical outcome (eg, any alcohol use at 30 days), and hierarchical linear modeling will be used to examine repeated measurements of alcohol use quantity and frequency, covarying for baseline levels of those variables and demographics. Hierarchical linear modeling is optimal for analyzing longitudinal data, as it allows for control over missing data and comparison of more than 2 waves of data [38,39].

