We hypothesize that those in the intervention group will have a lower proportion of individuals engaging in alcohol use at the postintervention and follow-up assessments compared to the control group. We also expect that individuals in the intervention group will report greater importance to avoid alcohol use compared to the control group at the postintervention evaluation and follow-up. Because this is a pilot study and we may not be powered to detect between-group differences, we will also explore changes within groups to determine whether there is potential for an effect (ie, a significant increase in their rating on the importance of avoiding alcohol use among the intervention group). We will explore potential differences between the intervention and control groups for our other outcomes, including proportion of individuals with hazardous drinking, attitudes toward drinking, psychiatric symptoms, and eating and lifestyle behaviors. Although we do not expect statistically significant differences given the small sample size, we hypothesize that those in the intervention group will show a direction toward improvement, and we will examine the effect sizes of the intervention.

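### Hazardous drinking, one exploratory outcome, is compared between arms only as a proportion above the AUDIT-C cut-off; a baseline-adjusted comparison of the score should be added beside it

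*Protocol article*

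**What the plan says.** Under Measures, Alcohol Use, the article says: "The presence of hazardous alcohol use will be measured with the Alcohol Use Disorder Identification Test-Consumption". The sex-specific rule follows: a "score of 3 or greater for women and 4 or greater for men indicates high risk for hazardous drinking". The same section makes a different variable primary: "The primary outcome is drinking status (ie, whether alcohol was consumed in the past 30 d").

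In the hypotheses under Results, the exploratory between-group comparisons are listed as "proportion of individuals with hazardous drinking, attitudes toward drinking, psychiatric symptoms, and eating and lifestyle behaviors". Hazardous drinking is the only item in that list expressed as a proportion.

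The Analytic Plan assigns chi-square and logistic regression to categorical outcomes at postintervention, and "analysis of covariance for continuous variables (controlling for baseline measurements") at the same time point. For the 6-month follow-up it adds hierarchical linear models of drinking quantity and frequency, with baseline levels and demographics as covariates. No analysis of the AUDIT-C score is named.

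**The concern.** A cut-off treats every patient below it as alike and every patient above it as alike. Participants and Procedures says that the sample is meant to include people who have not resumed drinking and people who have started but are unlikely to have a disorder yet. Many of their AUDIT-C changes could therefore occur below 3 or 4 and leave the hazardous-drinking outcome unchanged.

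The article says that the pilot's product for these outcomes is direction and effect size, used to judge whether a full trial is worthwhile. With 60 patients, a proportion based on few events gives an imprecise effect size. The score is already needed to apply the cut-off, and the plan already has a baseline-adjusted method for continuous variables. The outcome as named uses neither.

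**Working it through.** The article gives no power calculation, alpha, effect size or AUDIT-C distribution, so there is no stated figure to reproduce.

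**Inputs from the article.** Total N is 60 ("We plan to enroll 60 participants who underwent MBS"). The Results section expects at least 75% completion of each assessment: 0.75 × 60 = 45, or about 22 per arm.

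**Assumptions.** 1:1 allocation (30 per arm), two-sided 5% level, share p above the cut-off from 10% to 50%, baseline-follow-up correlation 0.5 or 0.7.

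**1. Information kept by a cut-off.** For a normal score split so that a share p lies above it, the efficiency relative to the full score is φ(z)² / [p(1 − p)], where z is the normal quantile at 1 − p.

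| p | φ(z)² / [p(1 − p)] | Kept | Lost | 60 × kept |
|---|---|---|---|---|
| 0.50 | 0.3989² / 0.25 | 0.637 | 36% | 38 |
| 0.30 | 0.3477² / 0.21 | 0.576 | 42% | 35 |
| 0.20 | 0.2800² / 0.16 | 0.490 | 51% | 29 |
| 0.10 | 0.1755² / 0.09 | 0.342 | 66% | 21 |

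The last column is the equivalent number of patients for this outcome only. The loss is near half only for p of about 20% to 25% (51% to 46%).

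**2. The same contrast as power.** With 30 per arm, a shift of (1.96 + 0.84) × √(2/30) = 0.72 SD gives the unadjusted score 80% power. The same shift gives the proportion 24%, 37%, 46% and 53% power at control rates of 10%, 20%, 30% and 40%. With 22 per arm the score has 67%, and the proportion 18%, 28%, 36% and 41%.

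**3. A more realistic score.** AUDIT-C is bounded and will have many zeros here, so the normal model is rough. A simulation used a discrete score with 30% to 60% zeros, 10% to 40% at or above a single cut-off of 3, 30 per arm, the same latent shift and 3,000 runs per setting:

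- proportion, unadjusted: power 21% to 54%;
- score, unadjusted t test: 53% to 71%;
- score, analysis of covariance on baseline: 59% to 89%.

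Setting by setting, using the score without adjustment gained 14 to 32 percentage points (smallest 39% to 53%, largest 21% to 53%). Baseline adjustment of the score added a further 6 to 20 points.

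**4. Event counts.** With 22 per arm and an assumed 10% in each arm, about 2 patients per arm are above the cut-off. The 95% half-width for the difference is 1.96 × √(2 × 0.10 × 0.90 / 22) = 0.18, larger than the rate itself. At 20% the figures are about 4 patients and 1.96 × √(2 × 0.20 × 0.80 / 22) = 0.24.

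**The case against.** The strongest reply is that the trial does not depend on this variable. Its main focus is feasibility, adherence and acceptability, and its primary alcohol outcome is 30-day drinking status. Hazardous drinking is one of several outcomes to be explored, and the article concedes limited power. That stands and sets the point's weight.

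Graded drinking data are also collected (drinking days, average and maximum drinks, days with 4 or more drinks, days drunk), and quantity and frequency are modelled with baseline covariates. A reader might infer that change below the cut-off goes unseen in this trial. It does not: those measures can show it. What remains is that the hazardous-use outcome itself cannot.

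Baseline control of the proportion is unstated rather than excluded, since logistic regression can take covariates. This matters for size. In a separate simulation (30 per arm, 0.5 SD shift, about 26% of controls at or above 3, correlation 0.6), unadjusted chi-square had 25% power and baseline-adjusted analysis of covariance 52%. A reader might conclude that the cut-off halves power, but that contrast mixes dichotomising with adjustment. Like for like, it was 25% against 42% unadjusted and 33% against 52% adjusted, a gap of 17 to 19 points.

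Finally, the proportion answers an interpretable question tied to the long-term goal of reducing the risk of hazardous use. In a sample with many non-drinkers, a mean score partly repeats any drinking versus none. That is a good reason to keep the proportion; it is no reason to leave the score unanalysed.

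**Conclusion.** The point holds as a modest gain in precision for one exploratory outcome. The article names hazardous drinking only as a proportion and states no baseline control for it at postintervention. Under a normal model the cut-off loses about 36% to 66% of the information in the score as the share above it falls from 50% to 10%. The share is assumed, the normal model is approximate, and the quantity and frequency models recover part of what is lost. The zero-heavy simulation agrees in direction in every setting tried.

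Two stronger readings are not supported:

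- That about half the information in the 60-patient pilot is discarded. The loss concerns one outcome, and about half requires roughly 20% to 25% above the cut-off, which the article does not give.
- That the article itself casts doubt on the 3/4 threshold because it mentions "the physiological changes postsurgery and how alcohol is metabolized differently". That phrase, under CBI Sessions, describes patient education and says nothing about AUDIT-C. Altered metabolism would also affect the meaning of the score, so it does not favour the score over the cut-off.

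Nothing in the article is contradictory here. A fuller analysis plan may already analyse the score, in which case the remedy is only to say so.

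**What to change.** In the Analytic Plan and in the list of exploratory outcomes under Results, add a between-group comparison of the AUDIT-C total score at postintervention. Use the analysis of covariance already planned for continuous variables, with baseline AUDIT-C as covariate. Report the adjusted difference with a confidence interval, robust or bootstrap because the score is skewed. Keep the proportion at or above 3 (women) or 4 (men) and report the two together.

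This assumes that AUDIT-C is collected at baseline and follow-up. Participants and Procedures and the Analytic Plan imply it, but no schedule by instrument is given, so this should be confirmed. If so, the change needs no new data, visits or patients, and completed enrollment is no obstacle. It is best made before results by arm are seen. The cost is one more exploratory analysis, of a skewed score.

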##### Other Alcohol-Related Measures

Using the importance ruler, participants will provide their rating of the importance of avoiding alcohol on a scale from 0 (not at all important) to 10 (very important). The Drinking Motives Questionnaire-Revised [31] assesses respondents’ reasons for drinking across 4 categories: conformity, coping, enhancement, and social. Each subscale consists of 5 items with responses ranging from 1 (strongly disagree) to 4 (strongly agree).

##### Psychiatric Symptoms

We will measure depression with the Patient Health Questionnaire-8 depression scale, which is a widely used, validated measure [32]. We will also assess anxiety with the Generalized Anxiety Disorder-7, which is commonly used to assess symptoms of anxiety [33]. Scores greater than or equal to 10 indicate a high likelihood of current depression or anxiety, respectively.

##### Eating and Lifestyle Behaviors

To explore the potential impact of the intervention on other important MBS-related outcomes, we will include measures related to eating and lifestyle behaviors. We will track the symptoms of food addiction using the Yale Food Addiction Scale 2.0 [34]. We will measure other eating behaviors with the Emotional Eating Scale [35] and the Eating Disorder Examination-Questionnaire [36]. We will also query about the frequency of lifestyle behaviors, including the use of a food diary, exercise, mindful eating, self-weighing, and obtaining 7 to 9 hours of sleep.

##### Study Feasibility

Feasibility will be assessed in several ways. First, we will calculate eligibility rates as the number who meet eligibility criteria divided by the number screened. Second, enrollment rates will be defined as the number of participants who enroll divided by the number eligible. To improve future recruitment strategies, we will record the reasons for nonenrollment. Finally, retention will be calculated using the rate of follow-up completion, as well as a determination of whether there was differential completion between the control and intervention groups.

##### Intervention Adherence

We will examine engagement with the intervention by examining the initiation and completion of CBI sessions and the response rate to the weekly poll questions.

##### Intervention Acceptability

We will use the Usability and Satisfaction Assessment to capture quantitative data on usability, overall satisfaction, helpfulness, content relevance, and use of intervention skills [37]. Items will query these areas for both the CBI sessions and SMS text messaging to examine acceptability of these components separately (ie, “I liked the 2-session computerized brief intervention,” “Is the content in the text messages relevant?” and “How helpful do you think the text messages were?”). The items will be rated on a 5-point scale and could be considered positive (ie, acceptable), neutral, or negative (ie, unacceptable). Exit interviews will provide qualitative feedback on intervention acceptability.

#### Analytic Plan

We will examine the frequencies of our feasibility, adherence, and acceptability variables. Although the primary focus is on feasibility and acceptability, we also plan to examine the direction of effects on outcomes. Our primary outcome is alcohol use. We will conduct chi-square and logistic regressions for categorical outcomes, and analysis of covariance for continuous variables (controlling for baseline measurements) to examine differences in outcomes between the intervention and control groups at the postintervention evaluation. For the 6-month follow-up, logistic regression will be used for the categorical outcome (eg, any alcohol use at 30 days), and hierarchical linear modeling will be used to examine repeated measurements of alcohol use quantity and frequency, covarying for baseline levels of those variables and demographics. Hierarchical linear modeling is optimal for analyzing longitudinal data, as it allows for control over missing data and comparison of more than 2 waves of data [38,39].

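### No baseline adjustment is specified for the binary primary outcome, although the plan specifies it for the continuous outcomes and the sample is deliberately mixed on baseline drinking

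*Protocol article*

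**What the plan says.** The Alcohol Use section under Measures defines a binary endpoint: "The primary outcome is drinking status (ie, whether alcohol was consumed in the past 30 d").

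For the postintervention comparison, the Analytic Plan says: "We will conduct chi-square and logistic regressions for categorical outcomes, and analysis of covariance for continuous variables (controlling for baseline measurements"). The remark about baseline stands directly after the analysis of covariance for continuous variables.

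For the 6-month follow-up, it says that "logistic regression will be used for the categorical outcome (eg, any alcohol use at 30 days"), with no covariate in that clause. The sentence then turns to a hierarchical linear model for "repeated measurements of alcohol use quantity and frequency, covarying for baseline levels of those variables and demographics". Read naturally, the variables meant there are quantity and frequency.

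Participants and Procedures shows that the sample is mixed on purpose. On the one hand, "This time frame was selected to engage patients who have not yet begun postoperative drinking"; on the other, the window is meant "to also engage individuals who began drinking, but are unlikely to have already developed AUD". Allocation is made "using urn randomization, separating participants by sex and time elapsed since MBS". Baseline drinking status is not among the balancing factors.

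**The concern.** The baseline value of the primary outcome is collected and is plausibly its strongest predictor, because someone who drank in the month before enrollment is more likely to report drinking three months later than someone who has not restarted. Yet it is the one outcome for which the article names no baseline control. The plan also does not say whether the chi-square or the logistic regression supplies the main estimate.

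Two things are at stake. The first is precision: variation that baseline status could explain stays in the error term. The second is chance imbalance. With about 30 per arm, one arm can easily start with several more drinkers than the other, and part of that gap passes into the outcome comparison. This matters even in a pilot, because Strengths and Limitations says that the direction of effects will help decide whether a fully powered trial is worth doing, and the Results section promises effect sizes.

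**Working it through.** The article gives no power, effect size or expected drinking rates, so there is no stated figure to reproduce. The calculations below are illustrative.

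**Inputs**
- From the article: 60 participants (Participants and Procedures), binary outcome, urn factors sex and time since surgery.
- Assumed: 1:1 allocation (30 per arm), no dropout, simple randomization, 40% drinking at baseline.
- Assumed follow-up drinking in controls, for baseline drinkers and non-drinkers respectively: a stronger link (85% and 25%) and a weaker link (75% and 30%).
- Assumed treatment effect, where one is used: odds ratio 0.25 within each baseline group.

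**Step 1. How likely is an imbalance?** If each participant has a 40% chance of being a baseline drinker, the chance that the arms differ by at least 10 percentage points (3 people of 30) is 51%, and by at least 20 points 15%. If exactly 24 of the 60 are baseline drinkers, the hypergeometric distribution gives 43% and 19%. The two differ because an even total of drinkers allows only even gaps, so the smallest gap that counts is then 4 people.

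**Step 2. What does an imbalance do?** With no treatment effect, the spurious outcome difference is (risk in baseline drinkers − risk in non-drinkers) × imbalance.
- Stronger link: (0.85 − 0.25) × 0.10 = 0.06, or 6 points per 10 points of imbalance.
- Weaker link: (0.75 − 0.30) × 0.10 = 0.045, or 4.5 points.

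**Step 3. What is the precision worth?** With no treatment effect, the unadjusted variance of the risk difference is 2p(1 − p)/30, where p is the overall risk. After adjustment, only the within-group variance w remains, giving about 2w/30.

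| | Stronger link | Weaker link |
|---|---|---|
| p | 0.4×0.85 + 0.6×0.25 = 0.49 | 0.4×0.75 + 0.6×0.30 = 0.48 |
| p(1 − p) | 0.2499 | 0.2496 |
| w | 0.4×0.1275 + 0.6×0.1875 = 0.1635 | 0.4×0.1875 + 0.6×0.21 = 0.2010 |
| SD unadjusted | 0.129 | 0.129 |
| SD adjusted | 0.104 | 0.116 |
| Variance ratio | 1.53 | 1.24 |

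Simulation with a Mantel-Haenszel risk difference stratified by baseline drinking, which allows for the small loss from uneven strata, gives ratios of about 1.5 and 1.2. Adjustment is therefore worth roughly 20% to 50% more participants.

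**Step 4. Risk of reading the wrong direction.** In simulation at an odds ratio of 0.25, the chance that the estimated risk difference is zero or favors control falls from about 6% to 2% (stronger link) and from about 2.5% to just over 1% (weaker link).

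**Step 5. Validity.** With no treatment effect, the unadjusted test rejected in about 5% of simulated trials. It is not biased over repeated randomizations.

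**The case against.** The case against has four parts.

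*The logistic covariates are unstated, not excluded.* A reader might infer that the plan fits logistic models without baseline drinking. The article does not say so. The baseline remarks sit inside joined lists and could be stretched to cover the regressions, and a logistic model with arm alone would largely duplicate the chi-square, which hints that covariates were intended. This stands, and it limits the point to what is specified. It does not remove the point: the article assigns baseline control model by model, the nearest reading leaves the primary outcome out, and no reading lets a chi-square adjust.

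*Covariate lists belong in the analysis plan.* Ordinarily so. Here, however, the article itself sets out which analyses control for baseline, and the asymmetry is in its own text.

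*The unadjusted comparison is sound and the design is not blind to drinking.* A reader might infer bias, or that baseline drinking is wholly uncontrolled. Neither is supported. Type I error stays near 5%. Time since surgery is an urn factor, and Participants and Procedures itself ties it to when drinking restarts, so some balance is built in. The imbalance probabilities above ignore this and are upper-end values.

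*This is a pilot.* Feasibility and acceptability come first, and the authors expect no significant differences, so power is a poor yardstick. That also stands, which is why the size is given as precision and direction. Nor do the documents support calling this the largest avoidable source of noise: attrition and self-report are not compared with it.

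**Conclusion.** The point holds as a gap in specification with a real but moderate cost. The article writes baseline control for the continuous outcomes and for quantity and frequency, and writes none for the outcome it calls primary. If the main comparison is left unadjusted, it remains valid on average but is less precise than it need be, and a chance imbalance in the single realized trial would go uncorrected.

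The size depends on how strongly baseline drinking predicts later drinking, which the article does not give. The range of about 20% to 50% more participants, and the fall in wrong-direction estimates to about 1%-2%, rest on the assumed 40% baseline prevalence, the two assumed links, 1:1 allocation and, for direction, an odds ratio of 0.25. The upper figures belong to the stronger link. A link weaker than 75% versus 30% would give less.

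**What to change.** State in the Analytic Plan that drinking status at the 3-month postintervention assessment and at the 6-month follow-up is analyzed by logistic regression on arm and baseline past-30-day drinking status. Name this as the main between-group estimate, reported with a 95% CI, and keep the chi-square as descriptive only. A marginal risk difference, which is easier to carry into planning a full trial, and a Firth penalty if cells are sparse are optional.

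The cost is one model term from data already collected at baseline, with no change for participants. Enrollment is complete, but the change can still be made, preferably before outcomes are compared by arm.
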